# The efficacy of a leukotriene receptor antagonist in the treatment of human rectal aberrant crypt foci: a nonrandomized, open-label, controlled trial

**DOI:** 10.1186/s12885-020-07266-6

**Published:** 2020-08-17

**Keywords:** Colorectal Cancer, Chemoprevention, Leukotriene receptor antagonist, Aberrant crypt foci

## Abstract

**Background:**

Leukotriene receptor antagonists (LTRAs) are broadly used for the management of allergic asthma and have recently been indicated to inhibit carcinogenesis and cancer cell growth. In colorectal cancer (CRC) chemoprevention studies, the occurrence of adenoma or CRC itself is generally set as the trial endpoint. Although the occurrence rate of CRC is the most confident endpoint, it is inappropriate for chemoprevention studies because CRC incidence rate is low in the general population and needed for long-term monitoring. Aberrant crypt foci (ACF), defined as lesions containing crypts that are larger in diameter and darker in methylene blue staining than normal crypts, are regarded to be a fine surrogate biomarker of CRC. Therefore, this prospective study was designed to explore the chemopreventive effect of LTRA on colonic ACF formation and the safety of the medicine in patients scheduled for a poly resection as a pilot trial leading the CRC chemoprevention trial.

**Methods:**

This study is a nonrandomized, open-label, controlled trial in patients with colorectal ACF and polyps scheduled for a polypectomy. Participants meet the inclusion criteria will be recruited, and the number of ACF in the rectum will be counted at the baseline colonoscopic examination. Next, the participants will be assigned to the LTRA or no treatment group. Participants in the LTRA group will continue 10 mg of oral montelukast for 8 weeks, and those in the no treatment group will be observed without the administration of any additional drugs. At the end of the 8-week LTRA intervention period, a polypectomy will be conducted to evaluate the changes in the number of ACF, and cell proliferation in the normal colorectal epithelium will be analyzed.

**Discussion:**

This will be the first study to investigate the effect of LTRAs on colorectal ACF formation in humans.

**Trial registration:**

This trial has been registered in the University Hospital Medical Information Network (UMIN) Clinical Trials Registry as UMIN000029926. Registered 10 November 2017.

## Background

Cancer is a one of the major health issues and a leading cause of death globally. The incidence, prevalence, and mortality rates of colorectal cancer (CRC) continue to rise all over the world [1, 2]. The majority of CRC cases are derived from adenomatous polyps [3], and their resection has been shown to reduce the risk of the future development of advanced adenomas and CRC [4, 5], thereby preventing CRC-related deaths [6]. However, patients with polyps (adenomatous polyps and/or hyperplastic polyps) represent a high-risk group for the occurrence of metachronous colorectal polyps and/or CRC [7]. Then, a paradigm is shifting from surveillance for the early detection of advance adenomas or CRCs and resection to novel tactics for prevention is required to reduce the mortality rate of this disease. A number of large-scale epidemiologic and/or clinical trials have assessed the prophylactic agents, including vitamin D, calcium, fiber and non-steroidal anti-inflammatory drugs (NSAIDs), such as aspirin and selective cyclooxygenase-2 (COX-2) inhibitors, in preventing against CRC development [8]. We previously reported that the NSAID sulindac suppressed the development of sporadic colorectal adenomas [9]. To this point, NSAIDS, particularly COX-2 inhibitors, have been proven to offer the greatest possibility for reducing CRC risk, either alone or in combination with other drugs [5], while it has been reported an elevated risk of serious cardiovascular events related with the administration of COX-2 inhibitors [10, 11]. In view of these adverse cardiovascular effects and the lack of efficacy of other drugs that initially looked promising, the development of novel agents that meet both safety and efficacy in preventing CRC is essential.

Leukotriene receptor antagonists (LTRAs), such as montelukast and zafirlukast, are commonly used for the treatment of allergic asthma [12, 13], and Tsai MJ et al. reported that LTRAs reduced cancer risk in a dose-dependent manner in asthma patients [14]. It was also reported that the cancer incidence rate was significantly lower in LTRA users than in non-LTRA users. (5.8 vs. 13.1 per 1000 patients/year). This means that apart from its role in asthma, LTRA has also been associated with carcinogenesis and tumor-mediated immunosuppression [15]. For example, the overexpression of cysteinyl leukotriene receptor 1 (CysLT_1_R) has been observed in CRC, and montelukast leads the apoptosis of CRC cancer cells [16, 17]. Previous in vivo studies have shown the chemopreventive effect of LTRAs [18, 19], but The chemopreventive effects of LTRA have not been studied in clinical practice. Therefore, we designed this study to ivestigate the chemopreventive effect of LTRAs in clinical practice. In CRC chemoprevention trials, the occurrence of adenomas or CRC itself is generally set as the trial endpoint. Though the occurrence of CRC is the most confident endpoint, it is not recommended for chemoprevention studies because CRC incidence rate is low in the general population and needed for long-term monitoring. Furthermore, there are ethical concerns about conducting long-term trials to determine whether a test agent is effective or not.

Aberrant crypt foci (ACF), defined as lesions containing crypts that are larger in diameter and darker in methylene blue staining than normal crypts [20–23], are regarded to be a fine surrogate biomarker of CRC [24]. Our group has previously reported that ACF is useful biomarker for CRC [25, 26] and study endpoint for a chemoprevention study [27, 28]. The advantages of chemoprevention studies with the number of colorectal ACF as the trial endpoint are that long-term observation is not needed to investigate the agent efficacy, and the number of ACF can be quantitatively estimated. Therefore, we set the ACF count as a good endpoint for this study. To the knowledge of us, this is the first clinical study investigating the use of LTRAs as chemopreventive agents against colorectal ACF in humans.

## Methods

### Study design and setting

This study was designed as a nonrandomized, open-label, controlled trial to be conducted in patients with colorectal ACF. It will be performed at the Department of Gastroenterology and Hepatology, Yokohama City University (YCU) Hospital, Japan. The coordinating office will be at the YCU Hospital, and patient registration will be conducted at the YCU center for novel and exploratory clinical trials (Y-NEXT) and data collection will be done using electronic data caputure.

### Ethical considerations and trial registration

The trial protocol complies with the Declaration of Helsinki [29] and the Ethical Guidelines for Clinical Research of the Ministry of Health, Labour, and Welfare, Japan [30]. Ethical approval of this trial was obtained from the Ethics committee of YCU Hospital on 30 May 2017. The study protocol and informed consent documents were approved by the YCU Hospital ethics committee. This trial has been approved in the Clinical Trial Act in Japan and registered in the Japan Registry of Clinical Trials (jRCT) as jRCTs031180094 and the University Hospital Medical Information Network (UMIN) Clinical Trials Registry as UMIN000029926. All study participants will submit a written study participation informed consent form.

### Participation criteria

We will recruit the patients with colorectal ACF and resectable polyps for this trial. The inclusion criteria are as follows: (1) patients with resectable polyps [adenoma, hyperplastic polyp, and sessile serrated adenoma/polyp (SSA/P)], (2) patients with more than five rectal ACF, and (3) submit written study participation informed consent form.

The exclusion criteria are as follows: (1) patients with lesions suitable for early removal, (2) a history of LTRA use within 2 months before study participation, (3) a history of malignant disease within 5 years before study participation, (4) a history of heart, renal, liver failure or liver cirrhosis, (5) a history of familial adenomatous polyposis, hereditary nonpolyposis CRC, or inflammatory bowel disease, (6) pregnancy or the possibility of pregnancy, (7) prohibitions of montelukast, (8) allergies to montelukast, (9) regular use of NSAIDs, metformin, and pioglitazone, and (10) participants considered as unsuitable for the study by the researchers.

### Intervention

All eligible participants will be assigned to the LTRA or no treatment group. Because this is an open-label trial, patients will be assigned to the no treatment group after the inclusion of patients in the LTRA group. Participants in the LTRA group will receive 10 mg of oral montelukast for 8 weeks, and those in the no treatment group will be observed without the administration of any additional drugs. At the end of the 8-week LTRA treatment period, a polypectomy will be performed to evaluate the changes in the number of ACF, and cell proliferation in the normal colorectal epithelium will be analyzed.

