### Sample size estimation and allocation

We previously reported the administration of 250 mg metformin per a day for 4 weeks reduced the number of ACF. In that trial, the mean number of ACF per patient decreased significantly from 8.8 ± 6.5 at baseline to 5.1 ± 5.0 at 4 weeks (*p* = 0.007) [28]. Although this study is exploratory research, and the accurate chemopreventive efficacy of montelukast is unknown, we assume that montelukast may have an effect that is equivalent to 60% of that observed for metformin on the reduction of ACF nubmer. Therefore, we estimate that the ACF number will change by about − 2 to − 3 on average. We determined that a sample size of 11–24 individuals in the LTRA group was needed to detect a significant reduction in the number of ACFs in the LTRA group using a paired t-test with a two-sided significance level of 5 and 80% power. Assuming some dropouts, we propose to recruit 30 participants in the LTRA group. To confirm that the number of ACF does not change during the study period, we propose to recruit 10 patients in the no treatment group after consecutively accumulating 30 patients in the LTRA group. Therefore, we propose to recruit 40 patients.

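### All 10 untreated patients enter after the 30 LTRA patients, so the between-group comparison can be attributed to the drug only if the two enrolment periods are assumed comparable

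*Protocol article*

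**What the plan says.** The protocol article (Study design and setting) describes the trial this way: "This study was designed as a nonrandomized, open-label, controlled trial to be conducted in patients with colorectal ACF". The order of assignment is given twice. Under Intervention: "Because this is an open-label trial, patients will be assigned to the no treatment group after the inclusion of patients in the LTRA group". Under Sample size estimation and allocation: "we propose to recruit 10 patients in the no treatment group after consecutively accumulating 30 patients in the LTRA group". The same section gives the controls their task: "To confirm that the number of ACF does not change during the study period".

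Four other statements bear on the point:

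- Participation criteria: entry requires more than five rectal ACF, and exclusion (10) removes "participants considered as unsuitable for the study by the researchers".
- Outcome measurements: the endpoint is each patient's change in ACF count over 8 weeks. The same endoscopists count at both examinations, and three blinded experts recount from the recordings.
- Statistical analysis: the change is compared between the LTRA and no treatment groups, by a test named as the paired t-test.
- Discussion: the limitations listed are the surrogate endpoint and the 8-week duration. The order of assignment is not among them.

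**The concern.** Patients 1 to 30 all receive montelukast and patients 31 to 40 all receive nothing. No control is enrolled in the same period as a treated patient, so no adjustment at analysis can separate the drug from the period. The arm is also certain before each patient is approached, while one exclusion rests on the researchers' judgement.

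The reason given does not lead to this order. An open label means that treatment is known once assigned; it does not require one arm to be filled first.

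The controls matter more than their number suggests. Patients are selected on a high value of the variable that is then measured again, so counts may fall on the second occasion through regression to the mean. The LTRA group's before-after test cannot tell such a fall from a drug effect. The 10 controls are the only element of the design that could, and they are drawn from another period. At stake is whether a difference between groups in 8-week change can be read as an effect of montelukast.

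**Working it through.** **1. Order of enrolment.** Both sections agree: 30 LTRA, then 10 controls. Arm is a deterministic function of enrolment number. Follow-up of the last LTRA patients may overlap the first controls by some weeks; enrolment does not.

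**2. The plan's own figure and the SD behind it.** The sample size section says "we estimate that the ACF number will change by about − 2 to − 3 on average" and obtains 11 to 24 LTRA patients "using a paired t-test with a two-sided significance level of 5 and 80% power". The SD of the change is not stated; only the SDs at each visit of the earlier metformin trial are given (6.5 and 5.0). Solving the paired t-test (noncentral t, two-sided 5%, 80% power) for the SD:

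- n = 24, change 2: SD = 3.35
- n = 11, change 3: SD = 3.20

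The stated range is thus consistent with an SD of change of about 3.2 to 3.4. This is an inference, used below as an assumption, with SD 5 as a wider alternative.

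**3. How far a non-drug period difference would carry.** Assume a two-sample t-test of the 8-week change, 30 v 10, no drug effect, and a period difference b in the mean change.

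- Standard error = SD × √(1/30 + 1/10) = SD × 0.365, which is 1.17 (SD 3.2), 1.24 (SD 3.4) and 1.83 (SD 5).
- Noncentrality = b / standard error; critical value of t on 38 df = 2.024.

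Two-sided false-positive rate (nominal 5%):

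| b (ACF) | SD 3.2 | SD 3.4 | SD 5 |
|---|---|---|---|
| 0.4 | 6.3% | 6.1% | 5.5% |
| 0.8 | 10.2% | 9.6% | 7.1% |
| 1.0 | 13.3% | 12.3% | 8.3% |

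**4. Where 0.4 to 0.8 comes from.** It is one possible mechanism, with assumed inputs. If mean baseline counts differ by 2 ACF between periods and the reliability r of the count is 0.8 or 0.6, the expected change differs by (1 − r) × 2 = 0.4 or 0.8 ACF. The assumed drug effect is 60% of the metformin fall, 0.60 × (8.8 − 5.1) = 2.22 ACF, so the shift is 0.4/2.22 = 18% to 0.8/2.22 = 36% of it. The 1.0 row is a further illustration with no mechanism behind it.

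**5. What 10 controls can show.** With SD 3.3, the 95% half-width for their mean change is 2.262 × 3.3/√10 = 2.4 ACF, larger than the lower end of the assumed effect (2). Even if the periods are comparable, evidence of no change will be weak.

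**The case against.** The strongest reply has five parts.

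- **Declared design.** The title says nonrandomized, and the text calls the work pilot and exploratory. That discloses the lack of randomisation. It does not explain non-concurrent controls, since concurrent non-random controls were possible.
- **The controls' purpose.** A reader might infer that the controls cannot serve their purpose at all, because they are observed after the period in which LTRA patients are treated. The documents do not support that. The Statistical analysis section uses study period for each patient's own 8 weeks, so the task is most naturally to show stability over 8 untreated weeks. Later controls can address this if the periods are comparable. This part stands.
- **Level shifts largely cancel.** A change in reader skill or case mix that is stable across a patient's two examinations mostly drops out of the within-patient change. The same endoscopists count both times, and there is a blinded recount. This also stands, and it narrows the concern to selection and to period differences in the change itself. Two endoscope models are named, but nothing suggests that their use shifts over time.
- **Limits on selection.** LTRA patients are accumulated consecutively, which restricts picking in that arm. It does not remove discretion exercised with the arm known.
- **Size.** A reader might infer a large inflation of error. No figure in the documents sets the bias. A baseline imbalance of 2 ACF could also arise under randomisation: with the metformin trial's baseline SD, the standard error of a 30 v 10 difference is 6.5 × 0.365 = 2.4. Randomisation makes such an imbalance chance, which the test's error rate allows for; a systematic period difference is not allowed for. Nor do the two-sample rates apply to the within-LTRA paired test on which the trial was sized.

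**Conclusion.** The point holds as a limit on attribution. Arm and enrolment period are completely confounded, assignment is known in advance, and the stated rationale does not justify either. A between-group difference in 8-week change can be credited to the drug only by assuming that the periods, and the patients entered in them, are comparable. The plan neither states that assumption nor lists it as a limitation.

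The size of any bias is unknown. The rates of about 6-10% for 0.4 to 0.8 ACF and 12-13% for 1.0 ACF rest on an SD inferred from the sample size range, on a two-sample test and on assumed period differences; with SD 5 they are about 5.5-7% and 8%. The structural conclusion needs none of these figures. The documents do not show that a period difference exists or that the control group is worthless.

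**What to change.** Keep 40 patients, the 30:10 split, the open label and the visits, but assign concurrently:

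- Interleave the control slots at 3:1 throughout recruitment, through the existing registration at Y-NEXT, preferably from a concealed random list. A fixed non-random interleaving, undisclosed to the enrolling endoscopist, is the minimum if the trial is to remain nonrandomized.
- Release each assignment only after the baseline ACF count is entered and eligibility, including exclusion (10), is locked.
- Delete the open-label rationale for the order of enrolment.

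The article does not give recruitment status; registration was in November 2017 and publication in August 2020. If recruitment is advanced, assign the remaining slots this way, and state as a limitation that the earlier LTRA patients have no concurrent control and that the between-group comparison is descriptive. If the LTRA arm is already full, only that statement is available.

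Cost: a protocol, ethics committee and registry amendment, consent wording on how assignment is made, and slightly later completion of the LTRA arm. A random list would also change the declared type of trial. No extra patients, visits or procedures are needed.

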### Drug supply

Montelukast capsules will be purchased from Kyorin Corporation Ltd., Tokyo, Japan. Participants will be informed to take one tablet of the study drug every night before bed. Medication adherence will be monitored by counting the empty medication sheets returned by the participants at the time of their polypectomy. The participants will also be interviewed and monitored to confirm that they have not used any prohibited drugs (aspirin, metformin, and/or other NSAIDs). AEs will be monitored by the investigator and graded according to the NCI-CTCAE version 4.0. If serious AEs or less than 80% drug adherence are confirmed in a participant, this participant will be withdrawn from the trial.

### Sample size estimation and allocation

We previously reported the administration of 250 mg metformin per a day for 4 weeks reduced the number of ACF. In that trial, the mean number of ACF per patient decreased significantly from 8.8 ± 6.5 at baseline to 5.1 ± 5.0 at 4 weeks (*p* = 0.007) [28]. Although this study is exploratory research, and the accurate chemopreventive efficacy of montelukast is unknown, we assume that montelukast may have an effect that is equivalent to 60% of that observed for metformin on the reduction of ACF nubmer. Therefore, we estimate that the ACF number will change by about − 2 to − 3 on average. We determined that a sample size of 11–24 individuals in the LTRA group was needed to detect a significant reduction in the number of ACFs in the LTRA group using a paired t-test with a two-sided significance level of 5 and 80% power. Assuming some dropouts, we propose to recruit 30 participants in the LTRA group. To confirm that the number of ACF does not change during the study period, we propose to recruit 10 patients in the no treatment group after consecutively accumulating 30 patients in the LTRA group. Therefore, we propose to recruit 40 patients.

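### The −3 end of the planned change, and the 11 patients derived from it, do not follow from the stated 60%-of-metformin assumption, which gives −2.2; the target of 30 is not undermined

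*Protocol article*

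**What the plan says.** All the relevant text is in the Protocol article, Methods, Sample size estimation and allocation.

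- **Reference effect.** In the sponsor's earlier metformin trial the mean count "decreased significantly from 8.8 ± 6.5 at baseline to 5.1 ± 5.0 at 4 weeks", with p = 0.007.
- **Assumed share.** Montelukast is taken to have an effect "equivalent to 60% of that observed for metformin on the reduction of ACF nubmer".
- **Inference.** "we estimate that the ACF number will change by about − 2 to − 3 on average", introduced as a consequence of the 60% assumption.
- **Sample size.** "We determined that a sample size of 11–24 individuals in the LTRA group was needed", for a within-group paired t-test at a "two-sided significance level of 5 and 80% power".
- **Recruitment.** 30 patients in the LTRA group, to allow for an unquantified number of dropouts.

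The SDs of 6.5 and 5.0 belong to the two time points. The article gives no SD of the within-patient change, no within-patient correlation and no size for the metformin trial.

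**The concern.** A stated percentage of a stated reduction is one number, yet the plan draws from it a range whose upper end is half as large again as its lower end. The sample size moves with the inverse square of the effect, so the choice of end more than halves the figure (24 down to 11). A reader who takes the derivation at face value will think that 11 patients can be enough under the 60% assumption.

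What is at stake is how the result is read. The plan allows patients to drop out of the analysis through low adherence, serious adverse events or a colonoscopy judged inappropriate. If losses were heavy, the low end of the printed range could be cited to call a small evaluable group adequately sized, and a null result could be given more weight than it deserves.

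**Working it through.** **Inputs from the article.** Metformin means 8.8 and 5.1; assumed share 60%; planned change −2 to −3; sample size 11–24; paired t-test, two-sided 5%, 80% power; 30 recruited.

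**Input not in the article.** The SD of the change. It is inferred below from the printed sample sizes and is therefore an assumption.

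**Step 1: the effect.**
- Metformin reduction: 8.8 − 5.1 = 3.7.
- Sixty per cent of it: 0.60 × 3.7 = 2.22.
- Lower end as a share of metformin: 2 / 3.7 = 54%.
- Upper end: 3 / 3.7 = 81%.

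This step needs no SD. The value 2.22 lies inside the range, 0.22 from one end and 0.78 from the other.

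**Step 2: reproduce 11 and 24.** Two formulas were tried, where δ is the change to be detected.

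*Normal approximation:* n = (SD × (1.960 + 0.842) / δ)², rounded up. At SD 3.45:
- δ = 3: (3.45 × 2.802 / 3)² = 10.4, so 11.
- δ = 2: (3.45 × 2.802 / 2)² = 23.4, so 24.

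Any SD from about 3.43 to 3.49 returns both printed figures.

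*Paired t-test, the test the plan names:* the smallest n with at least 80% power from the noncentral t distribution, with n − 1 degrees of freedom and noncentrality δ√n / SD.
- n = 11 at δ = 3 needs an SD of about 3.01–3.20.
- n = 24 at δ = 2 needs an SD of about 3.27–3.35.

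These intervals do not overlap, so no single SD gives both figures under the named test. At SD 3.43–3.49 the paired t-test needs 13 and 26. At SD 3.49 the printed pairs have about 73% power (11 at −3) and 77% (24 at −2).

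**Step 3: the same calculation at −2.22 (paired t-test).**

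| | SD 3.3 | SD 3.5 |
|---|---|---|
| n for 80% power at −2.22 | 20 | 22 |
| n for 80% power at −3 | 12 | 13 |
| n for 80% power at −2 | 24 | 27 |
| Power at −2.22 with 11 | 52% | 48% |
| Power at −2.22 with 24 | 88% | 85% |
| Power at −2.22 with 30 | 95% | 92% |
| Power at −2 with 30 | 89% | 86% |

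**Step 4: sensitivity to the SD.** If p = 0.007 came from a paired t-test on a mean change of 3.7, then SD = 3.7 × √m / t, where m is the unstated number of metformin patients and t is the two-sided 0.007 critical value on m − 1 degrees of freedom. Taking m from 9 to 15 as an assumed range:
- m = 9: SD 3.7 × 3 / 3.598 = 3.08. A change of −2.22 needs 18 patients.
- m = 15: SD 3.7 × 3.873 / 3.157 = 4.54. A change of −2.22 needs 35 patients, and 30 give about 74% power.

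The replacement number therefore has to come from the sponsor's own SD.

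**The case against.** The best defence is that the text is openly approximate. It calls the study exploratory, says the efficacy is unknown, and brackets 2.22 with the whole numbers on either side. The derived values lie inside the printed ranges: −2.2 within −2 to −3, and 20–22 within 11–24. The −2 end assumes less than 60% of metformin, so its 24 is cautious. The target of 30 exceeds even that. All of this stands. It does not explain −3: an effect of 81% is not a rounding of 60%, and the article presents the range as a consequence of the assumption.

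The mismatch between formulas is also small. It amounts to one to three patients and probably reflects a normal approximation; recruiting 30 absorbs it.

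Two stronger readings are tempting, and the article supports neither.

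- **That the trial has only about 50% power.** This pairs the sample size belonging to −3 with an effect of −2.2. The article never claims that 11 suffices at −2.2 and never makes 11 a target, a minimum evaluable number or a success criterion. Ending with 11–19 evaluable patients would mean losing 11–19 of 30 (37–63%), and nothing in the article suggests losses on that scale.
- **That 20–22 is the correct minimum.** Those figures rest on an SD back-solved largely from the very range in question. Step 4 shows how far they move under another route to the SD. The missing SD is not itself a fault here, since a full protocol may give it.

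**Conclusion.** The passage is wrong as written, but the error is minor. Sixty per cent of 3.7 is 2.2, so the −3 end and the 11 that comes from it contradict the plan's own assumption. That conclusion is plain arithmetic on printed figures. The remark that 11 and 24 share an SD only under a normal approximation rests on the two printed changes being the ones used for the two printed sizes, which the passage implies.

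The design is not undermined. For an SD of change of 3.3–3.5 (assumed), 30 patients give about 92–95% power at −2.2, and 24 completers still give about 85–88%. A materially larger SD would weaken that reassurance, but the article gives no basis for choosing one.

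**What to change.** In Sample size estimation and allocation:

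1. Replace the range of change by −2.2, shown as 60% of the 3.7 seen with metformin.
2. Give the paired t-test sample size for −2.2 at the sponsor's own SD of change, and print that SD. For illustration only, it is 20 at SD 3.3 and 22 at SD 3.5; neither should be adopted as a fixed threshold.
3. Remove 11 as a needed number. If −3 is kept, label it as an optimistic scenario at 81% of the metformin effect and give its own paired-t number (12–13 at those SDs).
4. Keep 30 recruited.

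This costs a rewording of about two sentences. Enrolment and the named test are unchanged. The only downside is a less favourable stated minimum.

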### Statistical analysis

The change in the number of ACF, which is the primary endpoint, will be compared before and after the 8-week study period between the LTRA and no treatment groups by the paired *t*-test. Drug safety will be assessed by the chi-square test, and the remaining results will be compared by the *t*-test or Mann–Whitney *U* test between the two groups. *P* < 0.05 will be defined as statistically significant. All statistical analyses will be conducted using JMP® 15 software (SAS Institute Inc., Cary, NC, USA).

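### The 80% power covers only the before-after test within the LTRA group, while the Statistical analysis section describes the primary comparison as between groups; the two sections must be reconciled

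*Protocol article*

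**What the plan says.** **Sample size estimation and allocation (Protocol article).** The effect is borrowed from an earlier metformin trial in which "the mean number of ACF per patient decreased significantly from 8.8" (SD 6.5) to 5.1 (SD 5.0). For montelukast, "we assume that montelukast may have an effect that is equivalent to 60% of that observed for metformin", and from this "we estimate that the ACF number will change by about" −2 to −3. The section concludes that "a sample size of 11–24 individuals in the LTRA group was needed". The purpose it gives for that number is a before-after comparison in one group: "to detect a significant reduction in the number of ACFs in the LTRA group using a paired t-test". The test level is 5%, two-sided, and the target power is 80%. Thirty patients are to be recruited to the LTRA group to allow for an unquantified number of dropouts. Ten untreated patients follow, as a check that ACF counts stay stable over the study period. No SD of change is given, and no power or precision is given for the 10 controls.

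**Statistical analysis (Protocol article).** The primary endpoint, change in ACF number, is to be compared before and after the 8 weeks "between the LTRA and no treatment groups by the paired" t-test. The remaining results are compared between the two groups by t-test or Mann–Whitney test. The significance threshold is P < 0.05.

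**The concern.** The two sections do not describe the same primary test. One powers a before-after change in a single group. The other places the primary comparison between two independent groups of 30 and 10, but names a test that applies only to paired observations. The title (a controlled trial) and the Discussion's remark about detecting differences between two groups both invite the between-group reading.

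The choice decides what the trial can conclude. Under the between-group reading, a drug with exactly the assumed effect of 2.2 would more often than not give a non-significant result. A reader who carried the 80% over to that comparison could take such a result as evidence against montelukast. This pilot is meant to lead to a larger chemoprevention trial, so that misreading would matter.

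**Working it through.** **1. Inputs.** From the sample size section: two-sided 5%, 80% power, change of 2 to 3, 11–24 in the LTRA group, 30 and 10 recruited, and metformin means 8.8 and 5.1 with SDs 6.5 and 5.0. These SDs describe counts at each visit, not the change. Assumed here: an SD of change (not stated), equal in both groups, and zero mean change in controls, which is the premise behind the control group.

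**2. Effect size.** Metformin effect: 8.8 − 5.1 = 3.7. Sixty per cent of that is 0.60 × 3.7 = 2.22. The upper value of 3 is 3/3.7 = 81% of the metformin effect.

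**3. Reproducing 11–24.**
- Normal approximation, n = ((1.960 + 0.842) × SD / δ)². At SD 3.45, δ = 3 gives 10.4, rounded up to 11, and δ = 2 gives 23.4, rounded up to 24. Both stated values are matched.
- Exact non-central t. SD 3.3 gives 12 and 24. No single SD gives both 11 and 24: n = 11 at δ = 3 needs an SD of 3.01–3.20, and n = 24 at δ = 2 needs 3.27–3.35.

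So 3.3 to 3.45 is a reasonable working range, but it is inferred.

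**4. What that SD implies.** SD² = 6.5² + 5.0² − 2ρ(6.5)(5.0) = 67.25 − 65ρ. SD 3.3 requires ρ = (67.25 − 10.89)/65 = 0.87. SD 3.45 requires ρ = (67.25 − 11.90)/65 = 0.85. A correlation of 0.5 gives √34.75 = 5.9.

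**5. Between-group power at 30 versus 10.** Two-sample t-test on changes: SE = SD × √(1/30 + 1/10), non-centrality δ/SE, 38 degrees of freedom, critical value 2.024.

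| SD of change | SE | δ = 2 | δ = 2.22 | δ = 3 |
|---|---|---|---|---|
| 3.3 | 1.205 | 36.6% | 43.5% | 68.0% |
| 3.45 | 1.260 | 34.0% | 40.4% | 64.1% |
| 5.9 | 2.153 | 14.6% | 17.0% | 27.4% |

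At SD 3.3 the difference detectable with 80% power is about 3.5, beyond the assumed range. The 95% CI half-width is 2.024 × 1.205 = 2.4 ACF.

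**6. Within-LTRA paired test at n = 30.** Non-centrality δ√30/SD, 29 degrees of freedom.

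| SD of change | δ = 2 | δ = 2.22 | δ = 3 |
|---|---|---|---|
| 3.3 | 89.4% | 94.5% | >99% |
| 3.45 | 86.6% | 92.6% | >99% |
| 5.9 | 43.5% | 51.4% | 76.9% |

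The within-group claim therefore holds at the inferred SD, but it too depends on an SD the plan does not state.

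**The case against.** The strongest defence is that the Statistical analysis sentence is ambiguous and its named test points the other way. A before-after comparison by paired t-test is a within-group analysis. The next sentence keeps ordinary between-group tests for the remaining results. The sample size section uses the same paired test and gives the controls only a stability role. Read this way, the primary test is the one that was powered, and 30 patients are enough. This stands: a power shortfall in the primary analysis is not established. It does not remove the problem, because the sentence also says the comparison is between the two groups, and both statements cannot hold.

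A reader might go further and infer that the trial's primary comparison has 37–68% power, or that the plan promises 80% for the group difference. Neither is supported. The first treats one reading as settled and a back-solved SD as the plan's own. As to the second, the 80% is tied explicitly to the LTRA group.

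It is also fair that the study is called exploratory and a pilot, and that "the accurate chemopreventive efficacy of montelukast is unknown". This lowers the stakes, but the plan still states a power and a significance threshold. Finally, the value of 3 does not drive enrolment: 24 covers a change of 2, 30 are recruited, and 2.2 lies within the stated range. The effect-size mismatch is a matter of clarity only.

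**Conclusion.** The point holds as a contradiction between two sections with a conditional consequence for power. The sample size section supports 80% for the within-LTRA before-after test only. If the between-group comparison is primary, power is below 80% across the assumed range: about 34–37% at 2, 40–44% at 2.2 and 64–68% at 3. These figures rest on an SD of change of 3.3 to 3.45, equal SDs, no change in controls and all 40 patients analysed. A larger SD lowers them (about 15–27% at SD 5.9), and so do dropouts, for which the plan gives no rate. That the group comparison falls short is robust to the choice of SD within this range; the exact percentages are not.

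**What to change.** **Statistical analysis section.** Name the within-LTRA paired t-test as the primary analysis, since it is the test that was powered. Compare the changes between groups by a two-sample method and report the difference as an estimate with its 95% CI (half-width about 2.4 ACF at 30 versus 10 with SD 3.3). Say that a non-significant group difference is not evidence of no effect.

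**Sample size section.** State the SD of change used and its source. Say that the 80% applies only to the within-LTRA test. Note that 60% of 3.7 is 2.2, so a change of 3 (n = 11) exceeds the stated assumption.

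**If the between-group comparison is kept as primary**, name a two-sample test and replace the 80% with the power that comparison actually has, under stated assumptions.

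**Cost.** A few sentences in two sections. Enrolment stays at 40. The stated power becomes less favourable for the group comparison. A within-group primary also carries a limit: patients enter with more than five ACF, so some fall on recount could occur without any drug effect. That is why the group difference should be reported beside it.
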